## Abstract

•Microvascular angina is a common cause of ischemia with non-obstructive coronary arteries (INOCA).•Endothelin-1 (ET-1) is a potent vasoconstrictor implicated in the pathophysiology of microvascular angina.•Zibotentan, an Endothelin Receptor Antagonist is being tested as a treatment for microvascular angina in the ‘PRIZE’ trial using a genetic ‘precision medicine’ approach.•The PRIZE ET Sub-study will provide a comprehensive genotype and phenotype bio-resource for microvascular angina patients.

Microvascular angina is a common cause of ischemia with non-obstructive coronary arteries (INOCA).

Endothelin-1 (ET-1) is a potent vasoconstrictor implicated in the pathophysiology of microvascular angina.

Zibotentan, an Endothelin Receptor Antagonist is being tested as a treatment for microvascular angina in the ‘PRIZE’ trial using a genetic ‘precision medicine’ approach.

The PRIZE ET Sub-study will provide a comprehensive genotype and phenotype bio-resource for microvascular angina patients.

## Introduction:

1

Ischaemic heart disease is the leading cause of premature disability and death worldwide, with stable angina pectoris the commonest symptomatic manifestation, affecting 112 million people [1], [2], [3]. Angina pectoris occurs due to a relative myocardial oxygen supply–demand mismatch, typically during physiological (e.g. exercise) or psychological stress. Historical teaching placed a causal link between obstructive epicardial coronary artery disease and angina. However, in patients undergoing coronary angiography with evidence of myocardial ischemia, the prevalence of non-obstructive coronary disease is reported in up to 70% with higher frequencies among women [2]. Cardiac ischemia in the absence of significant epicardial coronary stenosis is termed INOCA (Ischemia and No Obstructive Coronary Artery Disease). This group of patients experience long-term adverse outcomes including recurrent angina, cardiovascular death and myocardial infarction (MI) as well as lower quality of life and health anxiety causing repeated presentations to healthcare services [4], [5], [6], [7]. High quality trial data for drug therapy in this condition is lacking and standard anti-anginal therapy is unsatisfactory for many patients [2]. Based on previous studies of INOCA populations (typically excluding those whose ischemia is attributable to non-coronary cardiac or systemic diseases such as hypertrophic cardiomyopathy and valvular heart disease), it is estimated that in around two-thirds, coronary microvascular dysfunction (CMD) represents the underlying pathology [8], [9]. Microvascular angina is the name given for the clinical syndrome caused by CMD in these patients. The Coronary Vasomotion Disorders International Study (COVADIS) group have recently defined the diagnostic criteria for microvascular angina (Table 1) [10]. This definition of microvascular angina aligns with the term 'type 1 CMD' described initially by Camici and Crea [11]. The other principal INOCA endotype is epicardial vasospastic angina (VSA) which may co-exist with microvascular angina in some patients.

**Table 1 t0005:** COVADIS criteria for Microvascular Angina [10] used to identify patients eligible for PRIZE and the PRIZE ET Sub-Study. CAD indicates coronary artery disease; ECG, electrocardiogram; FFR, fractional flow reserve; Coronary CTA, CT coronary angiography; IMR, index of microcirculatory resistance; HMR, hyperemic microvascular resistance; SOB, shortness of breath; TIMI frame count refers to the scheme described by the Thrombolysis in Myocardial Infarction study group.

1. Symptoms of myocardial ischaemia	Effort angina or rest angina Angina equivalent e.g. SOB

2. Absence of obstructive CAD (>50% diameter reduction or FFR < 0.80) by	Coronary CTA Invasive coronary angiogram

3. Objective evidence of myocardial ischaemia	Ischemic ECG changes during an episode of chest pain Stress-induced chest pain and/or ischemic ECG changes in the presence or absence of transient/reversible abnormal myocardial perfusion and/or wall motion abnormality

4. Evidence of impaired coronary microvascular function	Impaired coronary flow reserve (cut-off values depending on methodology use between ≤ 2.0 and ≤ 2.5) Coronary microvascular spasm, defined as reproduction of symptoms, ischemic ECG shifts but no epicardial spasm during acetylcholine testing. Abnormal coronary microvascular resistance indices (e.g. IMR > 25, HMR ≥ 2.5 mm Hg·cm-1·s) Coronary slow flow phenomenon, defined as TIMI frame count > 25.
(4/4 = definite, 3/4 = probable diagnosis of microvascular angina)	

### Detecting and defining CMD

1.1

Given patency of the epicardial coronary arteries and adequate aortic pressure, coronary blood flow is regulated by dynamic changes in the resistance of the microvascular pre-arterioles and arterioles which are too small to be visualised on conventional angiography (diameter ≤ 500 µm) [12]. Multiple mechanistic sub-types of CMD have been proposed encompassing deleterious structural remodelling of the microvasculature as well as functional vasomotor abnormalities; however, in all cases, the fundamental abnormality is an inability of the coronary microvasculature to adequately match coronary blood flow to increased demand, such as during exercise [13].

CMD can be detected by invasive coronary guidewire based measurements of coronary blood flow, for example: Coronary Flow Reserve (CFR), which is the ratio of coronary blood flow during pharmacologically induced hyperemia to resting flow [12], [13]. Cardiovascular Magnetic Resonance (CMR) imaging additionally permits the non-invasive detection and quantification of CMD through the use of myocardial stress perfusion imaging with gadolinium contrast [14], [15]. Hyperemic myocardial blood flow (MBF) is measured during administration of adenosine and compared with resting blood flow to determine the myocardial perfusion reserve (MPR). This ratio of hyperemic to resting blood flow is analogous to CFR, and has prognostic value in CMD [16]. CMR has high spatial resolution, allowing differences between the epicardial and subendocardial blood flow to be accurately detected and quantified [17].

### Endothelin

1.2

Endothelin-1 (ET-1) is an endothelial peptide crucial for physiological regulation of vasomotor tone in coronary arteries [18], [19]. Increased circulating levels of ET-1 have been identified in patients with CMD [20], [21]. ET-1 is released from endothelial cells and causes potent and sustained vasoconstriction by binding to ET_A_ receptors expressed in vascular smooth muscle. These effects are counter-balanced in healthy individuals by the ET_B_ pathway, where vasodilators such as nitric oxide are released in response to ET-1 binding to endothelial ET_B_ receptors [22]. ET antagonists (across a spectrum of selectivity for ET_A_ versus ET_B_) have been investigated in a wide range of diseases. Clinical benefit has thus far, been best established in pulmonary arterial hypertension and three agents are currently licensed for this indication: bosentan, ambrisentan and macitentan [22].

Zibotentan (AstraZeneca, Cambridge, UK) is the most ET_A_ selective antagonist with high potency (pIC_50_ (negative logarithm of the half-maximal inhibitory concentration) for ET binding to ET_A_ receptors = 21 nM) [22] and is under investigation as a novel therapy for microvascular angina in the Medical Research Council's Precision Medicine with Zibotentan in Microvascular Angina (PRIZE) trial [23].

### Genetic dysregulation of Endothelin-1 and microvascular angina

1.3

The PRIZE trial is notable amongst cardiovascular clinical trials for defining eligibility by genetic analysis thus invoking a ‘precision medicine’ pathway whereby therapy will be targeted at those most likely to benefit. The genetic variant tested during screening for the PRIZE trial is the G allele of the rs9349379 SNP (single nucleotide polymorphism) found in the third intron of the PHACTR1 gene on chromosome 6. This variant has been linked to cardiovascular risk via enhanced Endothelin (EDN1) gene expression and is relatively common, with an estimated population frequency of 36% [23], [24]. In a sub-study of the British Heart Foundation Coronary Microvascular Angina (CorMicA) trial, patients with the rs9349379-G allele had significantly increased circulating concentrations of ET-1 as well as a higher likelihood of CMD, more myocardial perfusion defects on CMR, and decreased exercise tolerance when compared to patients without [25].

The principal aim of the PRIZE ET Sub-study is to identify additional novel, hitherto unknown functional genetic variants associated with microvascular angina, other than the rs9349379-G allele described above. For this reason, the study will run in parallel with the main PRIZE trial by preferential enrolment of the patients who are not selected after genetic screening for the rs9349379-G allele. Patient samples obtained in this parallel study will be genotyped using the UK Biobank Axiom^TM^ DNA Microarray. Briefly, the process involves extraction of DNA from whole blood, which is then denatured and fragmented, flourescentally labelled, and added to the array – a laborotary plate embedded with hundreds of thousands of DNA ‘probes’ (specific oligonucleotide sequences complementary to the genomic SNPs of interest). In the presence of a complementary DNA sequence, binding will occur by hybridization and scanning of the array for specific patterns of fluorescence can be used to identify genomic SNPs present in the patient's DNA [26]. In our study, analysis will be focused in the first instance, on SNPs located close to the gene encoding the ET_A_ receptor (EDNRA) with highly significant GWAS associations for ischemic heart disease, namely rs1878406 (Fig. 1) and rs6842241 (Fig. 2).

**Fig. 1 f0005:**
[figure not shown]
Phenome wide associations for rs1878406 with disease traits identified from the UK Biobank [30]. Traits (blue dots) above the red dotted line have a p value for association of < 1 × e^-8^. Chronic Ischemic Heart Disease (labelled) shows the strongest association. (For interpretation of the references to colour in this figure legend, the reader is referred to the web version of this article.)

**Fig. 2 f0010:**
[figure not shown]
Phenome wide associations for rs6842241 with disease traits identified from the UK Biobank[30]. Traits (blue dots) above the red dotted line have a p value for association of < 1 × e^-8^. Chronic Ischemic Heart Disease (labelled) shows the strongest association. (For interpretation of the references to colour in this figure legend, the reader is referred to the web version of this article.)

The rs1878406 SNP is located 8.5 kb upstream from the EDNRA gene on chromosome 4. The major rs1878406-C allele occurs with a frequency of 85% in Caucasian populations and is associated with cardiovascular risk, whereas the T allele is protective [27], [28]. The rs6842241 SNP is located 1.25 kb upstream from the EDNRA gene within the regulatory region. The risk allele (G) of rs6842241 has a frequency of 83% and is highly correlated (r^2^ > 0.8) with both rs1878406 and another SNP, rs6841581 located further upstream [29], which has been been identified in functional analysis as a possible epigenetic regulator of EDNRA gene expression [29].

We hypothesise that in a microvascular angina population, these SNPs related to the ET_A_ receptor, will result in greater ET_A_ receptor activation, reduced myocardial perfusion and more angina. Additionally, we wish to investigate whether higher ET_A_ receptor expression is associated with more severe disease, even amongst those without elevated circulating ET-1 levels.

## Methods and analysis

2

### Patient selection:

2.1

The PRIZE trial will invite up to 356 participants from 8 UK sites for genetic testing and eligibility for progression into the randomisation phase. In Cambridge, approximately 100 patients will be enrolled into the PRIZE study. Once the results of genotype analysis and other baseline screening tests are available, it is expected there will be 66 screen failures and these patients will be approached to continue in the PRIZE Endothelin (ET) sub-study rather than the main PRIZE study (Fig. 3). This will include genetic screen failures as well as those found to have exclusion criteria during clinical assessment. We anticipate most of these patients (n = 60) will re-consent for the sub-study.

**Fig. 3 f0015:**
[figure not shown]
Flowchart for PRIZE Endothelin (ET) Sub-Study (blue box). MVA corresponds to microvascular angina. (For interpretation of the references to colour in this figure legend, the reader is referred to the web version of this article.)

In Cambridge, patients will be initially identified from the Royal Papworth Hospital NHS Foundation Trust Microvascular Angina database as well as local participant identification centres and referring district general hospitals having met the definite or probable diagnostic criteria of microvascular angina as defined by the COVADIS group summarised in Table 1. Patients found to have the inclusion criteria for the PRIZE trial but subsequently excluded after genetic testing and baseline screening will be eligible for the PRIZE ET Sub-Study.

Participants may be screened out of the main PRIZE trial on the basis of their rs9349379 genetic sequencing blood test undertaken centrally in the NHS West of Scotland Centre for Genomic Medicine, Queen Elizabeth University Hospital, Glasgow. The patients and the researchers are blinded to the genotype. The result is then made available to the Clinical Trials Unit (Robertson Centre for Biostatistics, University of Glasgow). The PRIZE trial electronic case report form (eCRF) operates a 'genotype filter' which determines the participant's eligibility to continue in the main trial according to pre-determined, adaptively managed conditions with the final objective of achieving an overall 50% G allele frequency [23]. Participants who have been rejected by the genotype filter will be informed and then approached to participate in the PRIZE ET Sub-Study.

Participants may also have an exclusion criterion for the main PRIZE study (appendix A) during the first screening visit (i.e., before the results of the genetic blood test are available). For example, this may be because their total exercise time exceeds the maximum specified in the exclusion criteria. These participants will be offered the option of taking part in the PRIZE ET Sub-Study and the researchers will explain the rationale and study protocol. The participant will be allowed sufficient time to read the participant information sheet and ask any questions. If the patient provides informed consent, a venepuncture for the sub-study specific blood tests will be undertaken on the same visit.

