## Statistical consideration

3

For sample size calculation, we considered a difference of 1.0 mL·g^−1^·min^−1^ for stress MBF on CMR clinically significant with a pooled standard deviation of 0.56 based on previous published data [14]. Additionally, based on pilot data from our laboratory, we have assumed a difference in circulating plasma ET-1 between patient groups of 0.4 pg/ml with a pooled standard deviation of 0.36 to be clinically meaningful. Power calculations for an independent samples *t*-test demonstrate that a sample size of 60 (estimated to give 51 patients with the risk associated rs1878406-C allele) will have > 80% power to detect significant differences in both stress MBF and in plasma ET-1 between patient genotypes with a level of significance of 0.05 for an alpha error (SPSS, IBM Corp., USA).

Normality of continuous variable distributions will be assessed using the one sample Kolmogorov-Smirnov Test. Continuous variables will be summarised as mean ± standard deviation if normally distributed and median (Inter-Quartile Range) if non-normally distributed. Appropriate paired difference tests will be used to compare continuous variables according to the normality of the distribution. The primary outcome measure will be the difference in the circulating concentrations of ET-1 related peptides and ET_A_ mRNA between observed genotypes. Secondary outcome measures will be exploratory, including differences in disease burden measured by questionnaires, exercise tolerance tests and perfusion CMR between various ET_A_ SNP genotypes. Clinical trials unit and data management support and storage will be via the use of OpenClinica.

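### ET-1 and ET_A mRNA are compared across EDNRA genotypes without adjusting for rs9349379, which the article itself names as an ET-1 determinant: a modest loss of precision, not a bias

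*Protocol article*

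**What the plan says.** **Analysis (Protocol article, section 3).** "The primary outcome measure will be the difference in the circulating concentrations of ET-1 related peptides" and in ET_A mRNA, between genotypes. The sizing uses an independent-samples t-test: "a sample size of 60 (estimated to give 51 patients with the risk associated rs1878406-C allele) will have > 80% power". For ET-1 it assumes "a difference in circulating plasma ET-1 between patient groups of 0.4 pg/ml with a pooled standard deviation of 0.36". For the analysis it names difference tests chosen by the normality of the variable. (It calls them paired, which does not fit groups made up of different patients; that is a separate matter.) No covariate, stratum or regression model is mentioned.

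**Role of rs9349379 (section 1.3).** In an earlier cohort, "patients with the rs9349379-G allele had significantly increased circulating concentrations of ET-1". The same sentence links the allele to more microvascular dysfunction, more perfusion defects on CMR and lower exercise tolerance. No effect size or variance explained is given. The section sets the principal aim as finding variants other than this allele.

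**Entry to the cohort (sections 2.1 and 2.3).** Of the screen failures to be approached, the article says: "This will include genetic screen failures as well as those found to have exclusion criteria during clinical assessment". On the first route, "Participants who have been rejected by the genotype filter will be informed and then approached to participate in the PRIZE ET Sub-Study"; the filter is managed adaptively towards 50% G in the main trial. On the second route, patients with a clinical exclusion can join at the first visit, before their rs9349379 result is back. Stored samples from PRIZE participants at other sites may be added. Researchers are blinded to rs9349379, and the result goes to the Clinical Trials Unit.

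**The concern.** The article identifies a genetic determinant of its primary outcome and of two of its secondary ones (perfusion and exercise tolerance). It wants effects apart from that determinant, and part of its cohort is selected on it. The comparison it then describes ignores the determinant. Variation in ET-1 due to G count stays in the error term and widens the interval for the EDNRA effect. In addition, the plan's smaller group has only 60 - 51 = 9 patients, so the G count could differ noticeably between the EDNRA groups by chance. In that one realised sample, part of the observed ET-1 difference would belong to rs9349379 and could mask or mimic an EDNRA effect.

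**Working it through.** **Inputs from section 3.** ET-1 difference 0.4 pg/ml, SD 0.36; stress MBF difference 1.0, SD 0.56; groups of 51 and 9; alpha 0.05. Sidedness is not stated, so two-sided is assumed.

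**Assumption, not in the article.** R2, the share of ET-1 variance explained by G count, is taken as 0.05 to 0.20.

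**Step 1: the plan's own figure.** SE = SD x sqrt(1/n1 + 1/n2).
- ET-1: 0.36 x sqrt(1/51 + 1/9) = 0.130; noncentrality 0.4/0.130 = 3.07 on 58 df; power 85.6%.
- MBF: 0.56 x sqrt(1/51 + 1/9) = 0.202; noncentrality 1.0/0.202 = 4.94; power 99.8%.

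Both exceed the stated 80%, so the claim reproduces at 51:9.

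**Step 2: ET-1 power with rs9349379 as a covariate.** Residual SD = 0.36 x sqrt(1 - R2), with one further df lost. The 43:17 split is CC against T carriers: 60 x 0.85^2 = 43.35 CC, using the article's 85% C-allele frequency and assuming Hardy-Weinberg proportions.

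| R2 | Residual SD | Power 51:9 | Power 43:17 |
|---|---|---|---|
| Unadjusted | 0.360 | 85.6% | 96.8% |
| 0.05 | 0.351 | 87.3% | 97.4% |
| 0.10 | 0.342 | 89.0% | 98.0% |
| 0.20 | 0.322 | 92.2% | 98.9% |

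At R2 = 0 the adjusted power at 51:9 is still 85.6%, so the lost degree of freedom costs practically nothing. At R2 = 0.02 it is 86.3%.

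**Step 3: chance imbalance.** A 2-SD imbalance in G count moves the unadjusted difference by 2 x SE x sqrt(R2). At 51:9:
- R2 0.05: 2 x 0.130 x 0.224 = 0.058 pg/ml
- R2 0.10: 2 x 0.130 x 0.316 = 0.082 pg/ml
- R2 0.20: 2 x 0.130 x 0.447 = 0.116 pg/ml

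That is 15% to 29% of the 0.4 pg/ml target. At 43:17 (SE 0.103) it is 12% to 23%. Given such an imbalance, the false-positive risk of the unadjusted test is about 6.7%, 8.4% and 11.7% (normal approximation). These are conditional figures for an unlucky draw.

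**Step 4: bias and overall type I error.** rs9349379 is on chromosome 6 (section 1.3) and rs1878406 on chromosome 4 (text following Fig. 2). With the two loci simulated as independent (51:9, G frequency 0.36 or 0.15, R2 0.10 or 0.20, 8,000 runs each), type I error was 4.8-4.9% with and without adjustment, and mean bias was below 0.002 pg/ml in both. Only precision changed: the SD of the estimate fell from about 0.130 to 0.125 at R2 0.10, and to about 0.117 at R2 0.20.

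**The case against.** The strongest reply is that this is a preference about precision. Covariates are usually left to an analysis plan, and a condensed article need not list them. The t-test is named for sizing only, and nothing rules out an adjusted model. Chance imbalance is already paid for in the 5% error rate. The R2 range is assumed, and at 43:17 the gain is at most about 2 points. Preferential enrolment of patients turned away by the filter may also narrow the spread of G count, so that it explains less variance here than in an unselected cohort.

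Most of this stands, and it limits the size of the point. It does not remove it: the article does state how the comparison will be made, by difference tests chosen on normality alone, and that method does not use a determinant the article itself puts forward.

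Three stronger readings are tempting and are not supported:
- **Selection on rs9349379 biases the EDNRA comparison.** The filter acts on one locus and the comparison is at another, on a different chromosome. G count may vary by entry route or over time without confounding the EDNRA groups. Selection on disease or on exercise time could induce some correlation, but nothing in the article allows it to be sized.
- **Every participant already has a usable rs9349379 result.** The article does not say so. Clinical exclusions can enter before the result exists, and researchers are blinded to it. Likewise, only the filter route is selected on this variant.
- **rs9349379 is a strong source of ET-1 variance.** The article reports a significant association and gives no magnitude.

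**Conclusion.** The point holds as a modest improvement to a stated method. The unadjusted comparison gives up some precision and leaves the result open to chance imbalance in G count, in a design whose smaller group is 9 on the plan's own split. If R2 is 0.05-0.20, adjustment is worth about 2 to 7 points of ET-1 power at 51:9 and about 0.6 to 2 points at 43:17. Neither average bias nor inflation of the overall type I error is shown, and this point does not overturn the stated power above 80%. The figures rest on the assumed R2, a two-sided test, independence of the two loci and, for 43:17, Hardy-Weinberg proportions. The article links rs9349379 to ET-1 but not to ET_A mRNA, so the gain for mRNA may be nil. Whether 51:9 is itself the right split is a separate question that matters more for power.

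**What to change.** State the primary analysis as a linear regression of each biomarker (transformed if skewed) on EDNRA genotype, with rs9349379 G-allele count (0/1/2) as a covariate. Keep the unadjusted comparison as a sensitivity analysis.

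Take the G count from the PRIZE screening result held by the trials unit, released only after the laboratory measurements are complete so that blinding is preserved. Where no screening result exists, obtain the genotype from the stored sub-study DNA.

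The cost is one degree of freedom, plus the release and linkage of a blinded result. No further visit or blood sample is needed.
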